#### 3.3.2. Run-in phase

Children will be asked to maintain their usual sleep patterns for a 2-week period to capture their baseline sleep duration. It is expected that sleep duration may increase upon self-monitoring sleep, so the 2nd week of the run-in phase will define each participant's baseline sleep duration. If sleep duration measured by the sleep tracker is greater than or equal to 8.5 h per night on average during the second run-in week they will be excluded. In addition, if <2 nights of data are provided during the second run-in week, they will be excluded due to poor compliance. Otherwise, they will be randomized to a study condition for the optimization trial.

Additionally, baseline dietary intake will be captured during the 2nd week of run-in phase via three 24-h dietary recalls. A self-reported sleep diary will also be completed during the 2nd week of the run-in phase.

#### 3.3.3. Randomization and blinding

A computerized random number generated by the W2H platform will assign children to 1 of 16 study conditions. Block randomization will be used. Participants cannot be blinded to the interventions components to which they are exposed. The study coordinators will not be blinded because they will need to monitor intervention delivery and communicate appropriately with families. Investigators will be blinded, except the psychologist on the team who needs to direct the virtual study visit delivery for one of the intervention components.

#### 3.3.4. Intervention phase

Children will be randomly assigned to 1 of 16 conditions for a 6-month intervention phase. The study conditions differ with respect to sleep goal (guideline-based or personalized), digital sleep guidance (active or active with virtual sleep advisor phone calls), caregiver-directed incentive (inactive or active), and performance feedback (inactive or active). The study design includes one constant: all participants need to self-monitor their sleep duration by wearing the sleep tracker to allow for daily capture of sleep duration and goal achievement status. Dietary intake will be captured during the final month of the intervention phase via three 24-h dietary recalls. Sleep diaries will be completed by all participants for 1 week in months 2, 4, and 6. Participants will also complete monthly surveys at the end of each month.

#### 3.3.5. Visit 2

The caregiver and child will complete questionnaires. In addition, the child will complete anthropometric measures and a DXA scan. These measures will all be the same as those completed at Visit 1. This visit will be scheduled to occur 6-months after randomization, with a 4-week window in anticipation of scheduling issues.

#### 3.3.6. Follow-up phase

Participants will be asked to continue to wear the sleep tracker device to capture sleep patterns with all intervention components inactivated for ≈5.5 months follow-up phase. The purpose is to determine if any changes in sleep duration persist over time.

Dietary intake will be captured during the final month of the follow-up phase via three 24-h dietary recalls. Sleep diaries will be completed by all participants for 1 week in months 8, 10, and 12. Participants will also complete monthly surveys at the end of each month to continue to assess self-reported sleep data (PROMIS surveys) and mediators.

#### 3.3.7. Visit 3

The caregiver and child will complete questionnaires. In addition, the child will complete anthropometric measures and a DXA scan. These measures will all be the same as those completed at Visits 1 and 2. This visit will be scheduled to occur 12-months after randomization, with a 4-week window in anticipation of scheduling issues.

### 3.4. Study procedures and measures

#### 3.4.1. Anthropometry

Trained staff in CHOP's Nutrition and Growth Lab conduct standard body measurements. Height and weight will be measured first. From the height and weight data, a study staff member will verify that the child is eligible to proceed based on their BMI using the CDC's online calculator. If eligible to proceed, the remaining anthropometric measures, sitting height and waist circumference, will be completed.

#### 3.4.2. DXA scan

A DXA scanner will be used to measure the amount of fat, lean and bone tissue in each participant. This method uses a very low powered X-ray beam to scan the entire body. The whole-body scan takes <5 min. In the event of movement during the scan, technicians will attempt to repeat a scan up to two times (a total of 3 tries). The radiation used in this machine is very minimal. This is the standard method for measuring fat mass and body composition and is considered safe for children. Note, prior to having a DXA scan, a urine pregnancy test will be performed for female participants greater than or equal to 11 years of age and female participants younger than 11 years who are physically capable of becoming pregnant.

#### 3.4.3. Dietary recalls

Trained dieticians will call the participants three times during run-in (2^nd^ week), intervention (month 5), and follow-up phases (month 11). The participants will be asked to recall the foods and drinks they have consumed in the past 24 h. This dietary intake data will be entered into Nutrient Data System for Research (NDSR) to derive dietary patterns and estimates of energy, macronutrient, and micronutrient intake at the food, meal (which are time-stamped), day, visit, and participant levels.

#### 3.4.4. Sleep tracker

Sleep trackers will be issued at the baseline visit and will be worn for the duration of the study (approximately 1 year). Participants will be able to view some of their sleep tracker data on their W2H dashboard. All participants will see their sleep duration and the number of times they have met their sleep goal. Those in the performance feedback condition will also see more in-depth performance metrics (e.g., percentage of sleep goal achieved).

#### 3.4.5. Sleep diary

Participants will be asked to complete sleep diaries over 7 days during run-in (2^nd^ week), intervention (months 2, 4, and 6) and follow-up phases (months 8, 10, and 12). The sleep diary includes a “morning page” with 12 items to capture self-reported sleep health metrics (e.g., how well they slept last night) and an “evening page” with 5 items asking about alertness, nap times, and caffeine consumption during the day. The sleep diary will be sent via text message through REDCap using an encrypted, participant specific link. Twilio Cloud Communications will be used for texting.

#### 3.4.6. Child questionnaires

Research staff will assist children with the completion of their questionnaires at the in-person visits at baseline, 6-months, and 12-months. These questionnaires are broken into 8 sections: Sociodemographics and Home Environment; Bedroom Environment; Sleep and Chronotype; Screen Time and Social Media; Eating Behavior; School and Homework; Physical Activity; and Depression and Anxiety. The specific instruments included in the child questionnaires are listed in Table 4.

**Table 4 T4:** Instruments included in the child and caregiver questionnaires.

**Child questionnaires**	**Caregiver questionnaires**
Eating in the absence of hunger questionnaire (Tanofsky-Kraff et al., 2008)	Confusion, hubbub, and order scale (Chatterjee et al., 2015)
Evaluation of activity survey in youth (Pate et al., 2018)	Eating in the absence of hunger questionnaire (Tanofsky-Kraff et al., 2008)
Munich chronotype questionnaire (Zavada et al., 2005)	Epworth sleepiness scale (Johns, 1991, 1992)
PROMIS pediatric anxiety short form 8a (Irwin et al., 2010)	International physical activity questionnaire (Craig et al., 2003; Lee et al., 2011)
PROMIS pediatric depressive symptoms short form 8a (Irwin et al., 2010)	Morning-eveningness questionnaire (Horne and Östberg, 1976)
PROMIS pediatric sleep disturbance short form 8a (Forrest et al., 2018)	Physical activity neighborhood environment scale (Sallis et al., 2010; Ding et al., 2013)
PROMIS pediatric sleep-related impairment short form 8a (Forrest et al., 2018)	
School sleep habits survey (Wolfson et al., 2003)	
The hunger vital sign, U.S. household food security survey (Hager et al., 2010)	
Youth risk behavior survey (Control and Prevention, 2016; Mpofu et al., 2023)	

#### 3.4.7. Caregiver questionnaires

Caregivers will complete questionnaires during each in-person visit at baseline, 6-months, and 12-months. These questionnaires are broken into 7 sections: Sociodemographics; Pregnancy, Birth, and Infancy; Home Environment; Neighborhood Environment; Eating Behavior; Physical Activity; and Sleep and Health. The specific instruments included in the caregiver questionnaire are listed in Table 4.

#### 3.4.8. Monthly questionnaires

At the end of every month during the intervention and follow-up phases, caregivers will receive a text message with a link for 3 surveys in REDCap. These questionnaires include the Monthly Mediator Survey, Notable Events Form, and PROMIS sleep measures. If the participant did not complete any of these surveys the month leading up to the 6-month and 12-month in-person study visits, they will be administered at the in-person visit.

#### 3.4.9. Geospatial measures

Each participant's primary home address will be geocoded using ArcMap (v.10.5.1). To link built environment exposures, we will define each participants' residential neighborhood as: (1) the census block group in which their primary home is located, and (2) a half-mile buffer around their home address based on Euclidean (straight-line) distances. These definitions are being used because we expect that the built environment features influencing sleep will operate at close proximity. We will consider alternative buffers/neighborhood definitions in sensitivity analyses. The following geospatial measure will be calculated, but it is noted that these may be subject to change based on updated reference data sets and new data sets that become available.

##### 3.4.9.1. Sound levels

Sound data will be obtained from the US National Park Service Sound Map.^1^ The Park Service used random forest models to predict expected sound levels across the contiguous US on a typical summer day with calm conditions based on empirical acoustical data from 479 locations in national parks, urban and suburban areas. Their model incorporated geospatial features and was validated using leave-one-out cross validation (Mennitt and Fristrup, 2016). The specific sound metric used was L50 sound pressure level, which reflects the median sound level across all summer daytime seconds recorded for a given location after adjustment for the sensitivity of human hearing to very low and high frequencies (“A-weighting”).^2^ We will calculate neighborhood-level sound levels by taking the average sound levels in A-weighted decibels within a half-mile buffer of each participants' residence.

##### 3.4.9.2. Tree canopy cover

Data on tree canopy cover will be obtained from 2016 National Land Cover Database that was create by the US Forest Service.^3^ A raster file reflecting the estimated percentage tree canopy coverage at a 30-m resolution for the continuous US estimates were produced using random forest regression models incorporating multi-spectral Landsat satellite imagery and elevation data (Coulston et al., 2012). We will calculate the average percentage tree canopy cover within a half-mile buffer of each participants' home.

##### 3.4.9.3. Street connectivity

Street connectivity will be assessed by street density and intersection density using data obtained using Esri's 2016 StreetMap Premium (Esri, Redlands, CA). Street and intersection density will be calculated by dividing (1) the total linear meters of road in the half-mile buffer and (2) the total number of intersections in the buffer, by the buffer area in hectares.

##### 3.4.9.4. Population and housing density

Block group-level population density and housing density will be calculated using data from the 2012–2016 American Community Survey by dividing each participants' census block group population and number of housing units, respectively, by its land area in square miles.

##### 3.4.9.5. Neighborhood poverty

The percentage of residents in participants' home census tract with household incomes below the federal poverty limit will be calculated using the US Census Bureau's 2012–2016 American Community Survey data. These data will be retrieved from the IPUMS National Historical Geographic Information System (Manson et al., 2019).

#### 3.4.10. Candidate intervention components

The conceptual model showing each candidate component and their mediator is provided in Figure 1. For the sleep goal component, participants will be randomized to a condition that has either a guideline-based goal (≥9 h per night) or a personalized goal (+30 min per night above baseline). The sleep goal is specific to weeknights and the total number of times the sleep goal is achieved for each participant will be calculated.

For the digital sleep guidance component, participants will be randomized to receive text messages only or text messages with virtual sleep advisor phone calls. The text messages focus on evidence-based sleep health recommendations and focus span 6 domains: age-appropriate bedtime and consistency, schedules and routines, location, electronics, exercise and diet, and positivity and relaxation (Allen et al., 2016; Meltzer et al., 2021b). The sleep advisor phone calls will consist of three telephone calls of ≈15–30 min each during months 1, 2, and 5 of the intervention period. This brief intervention approach is modeled on previous sleep health education research (Quach et al., 2011; Corkum et al., 2016; Mindell et al., 2016). The calls in months 1 and 2 will be used to reinforce sleep health education and message content and to provide personalized guidance and problem-solving around overcoming barriers to increased sleep duration. The last call in month 5 will focus on how to sustain sleep health habits into the future. The sleep health sessions will narrow in on 1–2 barriers that are personally preventing a child from sleeping sufficiently.

For the caregiver-directed incentive component, participants will be randomized to receive or not receive a loss-framed financial incentive. If activated, caregivers will receive a financial incentive when their child achieves their sleep goal. The incentive will be loss-framed; caregivers will receive an endowment of $10 at the start of each intervention week, in a virtual bank account; we will deduct $2 each weeknight the sleep duration goal is not met; the funds remaining in the virtual account will be dispensed each Sunday. The weekly endowment-payment approach allows for fresh starts each week. The incentive will be directed at caregivers as a method to enhance engagement in helping their child to increase their sleep duration.

For the performance feedback component, participants will be randomized to receive or not receive detailed performance feedback metrics. All participants will be informed of their sleep duration. Those randomized to enhanced performance feedback will be able to view additional metrics on their W2H Dashboard and via text message, including sleep timing data, percentage of sleep goal achieved, shortest night of sleep, longest night of sleep. They will also be able to earn badges during the intervention in recognition of their progress. Badges will be sent via text message for (1) notable increases in sleep duration (i.e., bronze, silver, or gold medal badges for 1–15 min, 16–30 min, and >30 min average increases in sleep duration in the past week); (2) achieving their sleep goal for the first time; and (3) in recognition of the number of times they achieved their sleep goal in the past week.

### 3.5. Outcomes

#### 3.5.1. Primary outcomes

The primary outcomes are nighttime sleep duration (hours per night) on weeknights and fat mass index (kg/m^2^). Sleep duration will be estimated using the sleep tracker. Up to 260 weeknights (Sun-Thurs) and 104 weekend nights (Fri and Sat) of data will be captured per participant. Federal holidays and notable events (e.g., vacations) occurring on weeknights during the school term will be re-coded as weekend nights. Weeknights are the focus since insufficient sleep among children is more prevalent on weeknights.

Total body fat mass will be measured by DXA (Hologic Discovery A; Hologic Inc., Bedford, MA, operating in software version 13.5.3) at baseline, 6-months, and 12-months. Fat mass index (FMI, kg of fat divided by height in meters squared) will be calculated, and age and gender specific FMI Z-scores will be determined using U.S. specific FMI growth charts (Weber et al., 2013).

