### 3.7. Statistical plan

Under the intent to treat principle, we will use all available data and participants under the assumption of missingness at random. No participants will be excluded from the analysis except for the unlikely case of no outcome measurements for a participant. Final models will be adjusted for covariate dependent missingness due to dropout. We will examine sensitivity to the assumptions about the missing data mechanism.

#### 3.7.1. Aim 1

Mixed-effects linear regression models will be used to determine if the intervention components are associated with changes in weeknight sleep duration from baseline. The fixed model components will include indicators for each factor (with effect coding used to identify each component level), time in weeks, and all possible interactions between time and factors. The full model will be reduced to a more parsimonious model by selecting the main effects and interactions achieving a Type I error rate of alpha = 0.05.

#### 3.7.2. Aim 2

Mixed-effects linear regression models will be used to measures changes in fat mass index using the most parsimonious model from Aim 1 (i.e., optimal component settings for sleep promotion).

#### 3.7.3. Aim 3

The most parsimonious model from Aim 1 (i.e., optimal component settings for sleep promotion), will be expanded to determine if effectiveness differs by sociodemographic factors. The fixed model components will include indicators for each component (effect coding to represent the levels of each factor), time in weeks, the sociodemographic factor of interest, interactions between time, component(s), and sociodemographic factor. The sociodemographic factors that will be modeled include sex, race/ethnicity, and neighborhood context (poverty, sound, canopy cover, housing and population density, and street connectivity).

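### Summer-break Sunday–Thursday nights stay in the Aim 1 weeknight outcome and no model term tracks the school calendar, which costs some precision for smaller effects and interactions

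*Protocol article*

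**What the plan says.** Section 3.5.1 of the protocol article makes weeknight sleep duration a primary outcome: "The primary outcomes are nighttime sleep duration (hours per night) on weeknights and fat mass index". It then counts the nights: "Up to 260 weeknights (Sun-Thurs) and 104 weekend nights (Fri and Sat) of data will be captured per participant". Since 52 × 5 = 260 and 52 × 2 = 104, every Sunday–Thursday night of a 52-week year can enter the outcome, and no summer weeks are removed. The one adjustment for nights without school is limited to term time: "Federal holidays and notable events (e.g., vacations) occurring on weeknights during the school term will be re-coded as weekend nights". The reason for choosing weeknights is given as "Weeknights are the focus since insufficient sleep among children is more prevalent on weeknights".

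Baseline is a single week (section 3.3.2): "the 2nd week of the run-in phase will define each participant's baseline sleep duration". Section 3.7.1 describes the Aim 1 model: "The fixed model components will include indicators for each factor (with effect coding used to identify each component level), time in weeks", together with all interactions between time and factors. The model is then reduced by "selecting the main effects and interactions achieving a Type I error rate of alpha = 0.05". Section 3.7.3 extends the reduced model to the sociodemographic questions. Section 3.3.3 states block randomization and names no stratum for season.

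**The concern.** The re-coding rule implies that the sponsor expects sleep on nights without school to differ from sleep on ordinary weeknights. A single holiday in term is moved out of the weeknight outcome, yet a whole summer of such nights stays in.

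Each child is followed for about a year, so nearly every child meets a summer break. Whether it falls in the baseline week, the intervention or the follow-up depends on the enrolment date. Study week cannot stand in for this. At study week 10, a child enrolled in early autumn is in term, and a child enrolled in late spring is on summer break. A child with a summer baseline and a term-time intervention shows an apparent fall in sleep, and the opposite pattern shows an apparent rise.

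The components vary between children, so this variation enters the error of every component contrast. Random effects for child would relabel it as between-child variance but would not remove it. At stake is the precision of the screening step, because terms that miss 0.05 are dropped and the reduced model is carried into Aims 2 and 3.

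**Working it through.** **Inputs from the document.** SD 0.7 h, pre-post correlation 0.7, difference 0.5 h, alpha 0.05, power 0.80, all main effects and interactions, minimum N 41 (section 3.6.1); 325 randomized and 10% attrition (section 3.6.4), so 325 × 0.9 ≈ 292 completers.

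**Assumptions not in the document.** Summer nights longer by d = 20 to 60 minutes; a 10-week break; enrolment spread evenly over 52 weeks, or alternatively no baseline week in summer; 26 intervention weeks.

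**Step 1: reproduce the plan's figure.** The variance of change is 0.7² × 2 × (1 − 0.7) = 0.294 h² (1,058 min²). An effect-coded coefficient is half the difference, 0.25 h. With an F test on 1 and N − 16 degrees of freedom and noncentrality N × 0.25² / 0.294, the smallest N with 80% power is 41, as stated. So 0.294 h² is the plan's own yardstick.

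**Step 2: seasonal variance.** Let S be the share of a child's intervention weeks that fall in summer, and B equal 1 if the baseline week is in summer. The seasonal part of the change is d × (S − B).

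- B: probability 10/52 = 0.192, variance (10/52) × (42/52) = 0.1553.
- S: mean 0.192, range 0 to 10/26 = 0.385, variance 0.0276.
- Covariance of S and B: −0.0037.
- Var(S − B) = 0.0276 + 0.1553 + 2 × 0.0037 = 0.190.
- With no summer baselines, only S varies, and its variance among those enrolment dates is 0.0311.

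The excess is d² × 0.190 / 0.294 or d² × 0.0311 / 0.294, with d in hours. The standard error (SE) rises by the factor √(1 + excess).

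| d (min) | Excess variance, year-round baselines | SE rise | Minimum N | Detectable main effect at 292, 80% power | Excess variance, no summer baselines |
|---|---|---|---|---|---|
| 0 | 0% | 0% | 41 | 10.7 min | 0% |
| 20 | 7% | 3.5% | 43 | 11.1 min | 1% |
| 30 | 16% | 7.8% | 46 | 11.5 min | 3% |
| 40 | 29% | 13.5% | 51 | 12.1 min | 5% |
| 60 | 65% | 28.3% | 64 | 13.7 min | 11% |

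With a 12-week break the two variances become 0.223 and 0.0426. At 60 minutes the excess is then 76% and 14%.

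**Step 3: the run-in exclusion.** Section 3.3.2 excludes a child who averages 8.5 h or more in the baseline week, which removes more summer than term run-ins if summer sleep is longer. Assume a term mean of 7.5 h and SD 0.7 h. At d = 1 h the proportion passing is Φ(1/0.7) = 0.92 in term and Φ(0) = 0.50 in summer. Summer baselines fall from 19% to 0.192 × 0.50 / (0.192 × 0.50 + 0.808 × 0.92) ≈ 11%, and the excess falls from 65% to just under half.

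**Step 4: simulation of the 2⁴ design at n = 292.** The component estimates centre on zero under the null, so there is no bias.

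- With a 1.0 h difference and blocks filled in time order, the model SE is 0.082 h without a school-term covariate and 0.064 h with it. The actual sampling SE without it is 0.067 h, so the model overstates its own uncertainty. Type I error is 1.8%, and power for a 15-minute effect is 91% against 97%.
- With a 0.5 h difference and the same blocking, the model SE is 0.069 h against 0.063 h, and power is 96–97% either way.
- With simple randomization and a 1.0 h difference, power for a 15-minute effect is 86% without the term and 97% with it.

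**The case against.** The strongest reply is that this is only an omitted precision covariate in a short journal summary, and that an unseen analysis plan may add it. That stands in part. But the article does fix both the night-counting rule and the list of fixed effects, and the rule treats the same kind of night differently by time of year, so the point concerns what is written.

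The reply on harm is also largely right. The Aim 1 margin is wide, and power for a 30-minute main effect stays above 99.9% at 292 completers in every year-round case computed with differences up to 1.0 h. If blocks fill in time order, season is roughly balanced across conditions, and the result is conservatism rather than false selection. The planning SD and correlation come from earlier studies and may already carry some seasonal variation, so adding it in full may double count. The calculation uses one change score per child, a simplification of the weekly mixed model.

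A reader might infer two stronger things that the document does not support.

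- That the intended target is a school-night effect which summer nights contaminate. The text says weeknights throughout, and section 3.4.10 applies the goal to weeknights and the incentive to each intervention week with no summer exemption. A year-round weeknight outcome is a coherent choice.
- That summer dilutes a 30-minute effect to about 24 minutes (30 × 0.8). That requires the components to do nothing in summer, for which there is no evidence in the document.

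**Conclusion.** The point holds as one of precision and standard errors, not of bias, and not as a threat to the planned Aim 1 test. What rests on the text alone is that summer weeknights are in the outcome and that no listed model term follows the school calendar.

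The size is conditional on the assumed summer difference, break length and enrolment calendar. The lower range in the table applies if recruitment avoids summer run-ins. The year-round column is an upper range for a 10-week break, because it ignores the run-in exclusion and any seasonal variation already in the planning SD. In practical terms, the detectable main effect moves from 10.7 minutes to between 11.1 and 13.7 minutes in that upper range. This is a modest loss. It falls on the smaller main effects and interactions that the 0.05 screen has to sort.

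**What to change.** In sections 3.7.1 and 3.7.3, add two fixed effects: whether school is in session on each night (or in each week), and the same status for the second run-in week. State that both stay in the model whatever term selection removes. Take the status from the school calendar, so that it is fixed by date and cannot be affected by the assigned components. Most children will contribute both term and summer nights, so the seasonal difference is estimated largely within child.

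Keep the primary outcome as all Sunday–Thursday weeknights, as defined. Component-by-school-term interactions may be reported as supportive analyses only.

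The cost is a few sentences of analysis-plan wording and two covariates. Term dates are already needed to apply the re-coding rule, so no new data collection should be required, and the loss of degrees of freedom is negligible.
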